## Abstract

Background: Monitoring of motor function during surgery for supratentorial tumors under general anesthesia applies either transcranial electrical stimulation (TES) or direct cortical stimulation (DCS) to elicit motor-evoked potentials. To date, there is no guideline that favor one method over the other. Therefore, we designed this randomized study to compare between both methods regarding the prediction of postoperative motor deficits and extent of tumor resection. Methods: This is a multicenter (six centers in Germany and one in Switzerland), double blind, parallel group, exploratory, randomized controlled clinical trial. Patients without or with mild paresis, who are scheduled for surgical resection of motor-eloquent brain tumors under general anesthesia will be randomized to surgical resection under TES or surgical resection under DCS. The primary endpoint is sensitivity and specificity in prognosis of motor function 7 days after surgery. The main secondary endpoint is the extent of tumor resection. The study is planned to include 120 patients within 2 years. Discussion: The present exploratory study should compare TES and DCS regarding sensitivity and specificity in predicting postoperative motor deficit and extent of tumor resection to calculate the required number of patients in a confirmatory trial to test the superiority of one method over the other.

## 1. Introduction

Cancer of the central nervous system, with glioma being its most common histological type, was responsible for 721,787 disability adjusted life years (DALYs) in western Europe and 150,993 DALYs in Germany according to counts from 2016 [1]. Surgical resection is the treatment of choice for brain tumors in most cases. The goal is to achieve maximum tumor resection. This should be performed without or with only minimal postoperative neurological deficits in order to avoid relevant impairment of the quality of life of the patients after the operation, which can affect their ability to receive adjuvant therapy. Intraoperative monitoring is an established method to ensure the integrity of the corticospinal tract (CST) during surgical removal of brain tumors. It enables a so-called real-time monitoring, so that the surgeon can receive feedback on the integrity of the CST and the expected postoperative motor function during tumor resection and consider stopping resection, if necessary, to prevent postoperative deterioration of motor function [2,3]. Intraoperative monitoring can be performed during either awake surgery or general anesthesia. Awake surgery is usually preserved for intraoperative language monitoring. A recent survey conducted in 20 European centers revealed that 58.8% of the patients with brain tumors in eloquent areas were operated under general anesthesia [4]. While subcortical mapping is important to localize the CST during surgery for motor-eloquent brain tumors, monitoring of motor-evoked potentials (MEP) is the only way to assed its integrity and predict postoperative motor function when the surgery is performed under general anesthesia. During resection of brain tumors, MEP can be elicited by either transcranial electrical stimulation (TES) or direct cortical stimulation (DCS) [5]. Each method has its advantages and limitations. The advantages of DCS are the high focality of stimulation, the low stimulation intensity and smaller penetration of the electric field into white matter. The disadvantages are that DCS is not applicable before opening the dura or after closing it, it only allows the assessment of one hemisphere, its inability to insert the strip electrode under the dura in some cases (for example, recurrent tumors due to dural adhesion to the cortex) and possible dislocation of the strip electrode resulting in false positive results and/or time-consuming localization of the primary motor cortex. The advantages of TES-MEP are given by its surgeon-independent application, its availability throughout the surgery and assessment of the unaffected hemisphere for comparison. One of the disadvantages of TES is the possible deep penetration of electric current into the white matter after stimulation with high current intensities and/or using a less focalized electrode combination (for example C4/C3). This might cause a distant activation of the CST and potentially lead to false negative results. In some cases, the surgical approach itself, including skin incision and craniotomy, can interfere with the desired electrode position and, thus, limit the reliability of TES if non-optimal positions of the stimulation electrodes have to be used. This has led to the recommendation of the use of DCS when the motor cortex has to be exposed. For the decision on which method should by applied, neurosurgical units rely on the aforementioned considerations, as well as the individual surgeon’s and neuromonitoring staff’s experience and preferences. Tumor resection under monitoring of MEP has been reported in several studies using DCS [6,7,8] or TES [9,10], with a wide range of sensitivities and specificities for predicting postoperative deficits [6,9,11]. In addition to the different stimulation modalities, there are different alarm criteria to predict postoperative deterioration of motor function [11]. The accuracy of predicting postoperative deficits has a significant impact on clinical outcome, because false negative results (no significant intraoperative MEP change but a postoperative motor deficit) might lead to an unexpected deterioration of motor function, while false positive results (significant intraoperative MEP change without postoperative motor deficit) might lead to an unintended incomplete tumor resection. In addition, the outcome of the operation determines the postoperative quality of life, which has been shown to also affect the patients’ ability to receive adjuvant therapy [12,13]. Because neither the impact of the stimulation modalities nor that of the alarm criteria on postoperative motor function and extent of tumor resection has been investigated yet, we designed the TRANSEKT trial: a multicenter randomized double blind controlled exploratory study which will compare TES-MEP with DCS-MEP for monitoring of MEP in patients undergoing resection of brain tumor under general anesthesia. The aim of this first study is to calculate the required number of patients in a confirmatory trial to test the superiority of one method over the other.

## 2. Methods

### 2.1. Trial Design

This is an interventional, multicenter, double blind, parallel group, exploratory, randomized controlled clinical trial. Eligible patients are randomized to a surgical resection under TES (the intervention arm) or surgical resection under DCS (control intervention).

### 2.2. Objectives

The main aim of the trial is to gain knowledge about the sensitivity and specificity of each transcranial and direct cortical stimulation in prognosticating postoperative deterioration of motor function. This is necessary to calculate the required number of patients in a confirmatory trial to test the superiority of one method over the other. The trial is also designed to study the effect of stimulation modality on the rate of postoperative paresis and extent of tumor resection. A further objective of the trial is to assess functional impairment using Karnofsky performance scale and Barthel index, as well as health-related quality of life using EORTC QOL C30 and the simplified Beck Depression Inventory (BDI-S) in patients undergoing surgery for motor-eloquent brain tumors.

### 2.3. Participating Centers and Recruitment

The following neurosurgical departments intend to participate: University Medical Center Göttingen (UMG), Charité University Clinic, Berlin (CUB), University Medical Center Mainz (UMM), University Medical Center Würzburg (UMW), Klinikum rechts der Isar, School of Medicine, Technische Universität, München (TUM), Ludwig-Maximilians-University, Campus Grosshadern, Munich (LMU) and Inselspital, University Hospital, Bern, Switzerland (UHB). Patients will be recruited for the study from the neurosurgical outpatient clinic or through referral from regional hospitals. The intended recruitment rate will be one to two patients/month per center.

### 2.4. Inclusion Criteria

Age ≥ 18 and ≤80 years.Ability to give informed consent.Indication for surgical resection of a supratentorial tumor.Suspected supratentorial glioma or metastasis in close vicinity to the CST confirmed in a preoperative magnetic resonance imaging (MRI).Missing or mild preoperative paresis; Medical Research Council scale for muscle strength (MRC) grades 5 or 4.

### 2.5. Exclusion Criteria

Tumor infiltration of the precentral gyrus.Unavailable preoperative MRI.Severe preoperative paralysis (MRC grades 1, 2 or 3).One of the stimulation modalities is not appropriate for intraoperative application according to the neurosurgeon.

### 2.6. Study Timeline

The flow diagram (Figure 1) depicts study interventions and follow-up time points. In sum, evaluations take place by the time at hospital admission upon screening for including the patients in the study, 24 h after surgery, at discharge or 7 days after surgery and at the follow-up visit 3 months postoperatively. The motor status measured by MRC, the Karnofsky performance scale, the Barthel index, the EORTC QOL C30 and the BDI-S will be assessed preoperatively. After these baseline assessments, patients will be allocated randomly to tumor resection under intraoperative monitoring using either the TES or DCS for MEP evaluation. The motor status is assessed 24 h after surgery. The extent of resection will be assessed on postoperative MRI performed within 72 h after surgery. The motor status measured by MRC, Karnofsky performance score and the Barthel index will be assessed at discharge or 7 days after surgery and at follow-up visit 3 months postoperatively, while EORTC QOL C30 and BDI-S will be assessed a second time during a follow-up visit 3 months postoperatively. We expect to complete patient inclusion in twenty-one months. The estimated duration of the study (including follow-up) will be 2 years.

### 2.7. Interventions

#### 2.7.1. Anesthesia

Each participating center should follow its local standard procedure, which applies for all included patients in both arms of the study at that specific center. The following points apply for all participating centers:All procedures are performed under general total intravenous anesthesia.Muscle relaxant (e.g., rocuronium bromide) is applied for intubation only.Anesthesia is induced using propofol and continued using perfusion pumps. Analgesia is applied using sufentanil for the intubation and maintained through remifentanil.Use of an infusion pump with TCI function (target-controlled infusion) for maintaining anesthesia and analgesia during surgery is recommended.Invasive measurement of blood pressure is performed to maintain stable systolic and mean blood pressure. Body temperature is kept at norm values.Monitoring of the depth of anesthesia using EEG Monitoring is recommended.Performing regional scalp block or local infiltration at the headframe pins is recommended.

#### 2.7.2. Installation of Intraoperative Monitoring

Installation of intraoperative monitoring starts after intubation and is identical in both study arms. Patients are put in a supine position. Metal pins are used for head fixation, and proximity to the installed electrodes is avoided.

Transcranial electrical stimulation: corkscrew-like electrodes are placed subcutaneously at C1, C2, C3, C4, and Cz according to the international 10–20 electroencephalography system. Skin incision is tailored to avoid interfering with the installed electrodes and, if necessary, sterile electrodes are placed close to the skin incision. The combination C4 to Cz (anode/cathode) is used for stimulation of the left half of the body and C3 to Cz for stimulation of the right half of the body. If a proper stimulation of the lower extremities is not possible with a C3/C4-Cz combination, a C2 to C1 stimulation can be applied for the left leg and C1 to C2 for the right leg.

Direct cortical stimulation: after craniotomy and opening the dura, a strip electrode with four contacts is placed subdurally. Its position is changed until the primary motor cortex can be stimulated through one of the four contacts. Performing phase reversal is allowed on the surgeon’s indication. In addition, presurgical localization of motor cortex and CST using functional imaging or transcranial magnet stimulation can be performed if it is part of the clinical routine at the participating study site [14].

Stimulation parameters: a train of five consecutive pulses with an interstimulus interval of 2–4 ms and an individual pulse width of 0.5 ms pulse duration is applied. The stimulation intensity of DCS is limited to 25 mA according to safety recommendations and the maximum possible stimulation intensity for TES depends on the stimulator output.

Recording of MEP: pairs of subdermal needle electrodes are bilaterally inserted in the following muscles: biceps brachii, extensor digitorum, abductor pollicis brevis, quadriceps femoris, tibialis anterior and abductor hallucis muscles.

#### 2.7.3. Intraoperative Monitoring

A baseline measurement for each muscle is carried out after dural opening with determination of the stimulation threshold for the transcranial MEP or the stimulation threshold and the amplitude for the direct cortical MEPs. During tumor resection, MEP stimulation is performed at least every two minutes for to the randomized method and every 10 min for the other method. The surgeon is informed if a significant MEP deterioration according to the randomized method occurs, and that in case of persistence of the alteration, a significant deterioration of the postoperative deterioration of motor function is to be expected. At the end of the procedure, a final measurement of the stimulation threshold for the transcranial MEP or the stimulation threshold and the amplitude in the direct cortical MEPs is performed.

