### 2.10. Blinding

Neither the patient nor the neurosurgeon will be aware of the applied monitoring method during tumor resection. If randomized to TES, detection bias resulting from a possible dislocation of the strip electrode will be minimized through regular impedance measurement (every 2 min) and through performing DCS every 10 min. The medical technical assistant who performs the intraoperative monitoring is blinded to the motor outcome and those who assess the motor outcome are blinded to the intraoperative monitoring.

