#### 2.13.1. Primary Endpoint

The sensitivity and specificity of the transcranial and direct cortical stimulation with regard to motor deficit at discharge or 7 days after the operation are calculated and compared between the procedures using the Farrington-Manning test. Sensitivity refers to the probability of having a motor deficit at discharge (or 7 days after surgery), after reaching a predefined deterioration of MEP according to the applied alarm criterion during tumor resection. Specificity refers to the probability of not having a motor deficit at discharge (or 7 days after surgery) while not reaching a predefined deterioration of MEP according to the applied alarm criterion during tumor resection. The sensitivity is tested for superiority to a two-sided significance level of 5%; the specificity is tested for non-inferiority with a non-inferiority threshold of 10% with a one-sided significance level of 2.5%. One method is superior to another if it has been possible to demonstrate superiority in sensitivity and non-inferiority in specificity (intersection hypothesis). A correction of control of the type I error is, therefore, not necessary. Despite the conservative design, the main aim of the study is to gain a first understanding of the underlying differences in prognostic sensitivity and specificity between the two procedures.

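### The plan records both MEP methods in every patient but does not settle which readings enter the primary comparison; the named unpaired test and the stated precision do not fit each other

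*Protocol article*

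**What the plan says.** All places are in the protocol article.

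- **Both methods in each patient.** Section 2.7.2: "Installation of intraoperative monitoring starts after intubation and is identical in both study arms". Section 2.7.3: "MEP stimulation is performed at least every two minutes for to the randomized method and every 10 min for the other method". Section 2.5 excludes patients in whom either modality is unsuitable.
- **Only one method is acted on.** Section 2.7.3: "The surgeon is informed if a significant MEP deterioration according to the randomized method occurs". For the TES arm, section 2.10 gives the second method a checking role: bias from strip dislocation is to be limited "through regular impedance measurement (every 2 min) and through performing DCS every 10 min".
- **Primary analysis.** Section 2.13.1: sensitivity and specificity "are calculated and compared between the procedures using the Farrington-Manning test", with a positive result defined as "after reaching a predefined deterioration of MEP according to the applied alarm criterion during tumor resection". No paired analysis is mentioned.
- **Aim.** Section 2.2: to "gain knowledge about the sensitivity and specificity of each transcranial and direct cortical stimulation in prognosticating postoperative deterioration of motor function", so that a confirmatory trial can be sized.
- **Precision.** Section 2.11 states that 110 patients give 95% interval widths of 29 points (sensitivity difference) and 13 points (specificity difference), and calls this sufficient for planning.

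**The concern.** Each patient yields two index-test results, TES and DCS, against one reference outcome, the change in MRC grade at discharge or day 7. The named test treats the two methods as if they came from different patients.

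Either reading of section 2.13.1 leads to a conflict. If only the randomised method counts, each method is judged on about half the deficits, and the precision in section 2.11 is out of reach. If both methods count in every patient, the precision is about right but the test ignores the pairing.

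The between-arm contrast has a further weakness. Sensitivity is computed among patients with a deficit, which arises after randomisation. The alarm that is acted on can influence who develops one. Randomisation therefore does not make the deficit patients of the two arms comparable.

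At stake is the main product of the trial: estimates precise enough to size the next one.

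**Working it through.** **Inputs.** Section 2.11: 110 evaluable patients, deficit prevalence 30%, TES sensitivity and specificity 0.99 and 0.99, DCS 0.80 and 0.95. Section 2.9: 1:1 allocation. Section 2.13.1: two-sided 5% for sensitivity. The correlation between methods is not given, so its feasible range is shown.

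**Counts.** Deficits: 110 × 0.30 = 33; non-deficits: 77. Split over two arms: 16.5 and 38.5 per method.

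**1. Reproducing 29 and 13 with an unpaired analysis.** Wald width = 2 × 1.96 × √[p1(1−p1)/n + p2(1−p2)/n].

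- Sensitivity, n = 16.5: 3.92 × √(0.0099/16.5 + 0.16/16.5) = 3.92 × √0.01030 = 39.8 points.
- Specificity, n = 38.5: 3.92 × √(0.0099/38.5 + 0.0475/38.5) = 3.92 × √0.001491 = 15.1 points.

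No interval method that was tried gives the stated pair with 55 patients per arm. All patients counted for each method come close:

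| Method | 55 per arm: sens / spec | All 110 per method: sens / spec |
|---|---|---|
| Wald | 39.8 / 15.1 | 28.1 / 10.7 |
| Agresti-Caffo | 44.4 / 19.5 | 30.1 / 12.4 |
| Newcombe | 47.2 / 22.3 | 31.5 / 13.7 |
| Farrington-Manning | 46.1 / 22.2 | 30.0 / 13.5 |
| Miettinen-Nurminen | 47.0 / 22.4 | 30.2 / 13.6 |

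With 120 patients counted for each method, Miettinen-Nurminen gives 28.7 / 12.8, which rounds to 29 / 13. The stated precision therefore fits about 33 deficits and 77 non-deficits per method, twice what randomised arms supply.

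**2. Paired analysis of all 110 patients.** Wald width = 2 × 1.96 × √[(p1 + p2 − 2·p11 − (p1 − p2)²)/n], where p11 is the probability that both methods are correct.

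- Sensitivity, n = 33: p11 = 0.80 (maximum overlap) gives 3.92 × √(0.1539/33) = 26.8; p11 = 0.792 (independence) gives 28.1; p11 = 0.79 (minimum) gives 3.92 × √(0.1739/33) = 28.5.
- Specificity, n = 77: p11 = 0.95 gives 3.92 × √(0.0384/77) = 8.8; p11 = 0.9405 gives 10.7; p11 = 0.94 gives 3.92 × √(0.0584/77) = 10.8.
- Tango score intervals, from maximum overlap to independence: 28.7 to 30.7 (sensitivity) and 11.9 to 13.6 (specificity).

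Wald is optimistic with proportions this near 1, so the Tango figures are the safer guide. They are about equal to the stated 29 and 13, not clearly better.

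**3. Power for sensitivity, 99% against 80%.**

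- Unpaired score test by enumeration: 35% with 16 deficits per arm, 40% with 17. A normal approximation at 16.5 gives about 43%.
- McNemar with 33 pairs by enumeration, from independence (discordant probabilities 0.198 and 0.008) to maximum overlap (0.19 and 0): exact 58-62%, mid-p 72-78%, uncorrected asymptotic 80-90%.

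**The case against.** A reader might infer that the plan uses only the randomised method and throws away half of its accuracy data. The documents do not support that as stated.

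- **It is inferred, not written.** No sentence excludes the other method's readings. Section 2.13.1 compares procedures, whereas section 2.13.2 speaks of randomisation groups for secondary endpoints. The widths in section 2.11 even suggest that every patient may count for both methods. The test and the wording on the applied criterion favour the narrower reading, as does section 3, which ties each criterion to a study arm. They do not settle it.
- **The second readings are not equivalent data.** They are taken about one fifth as often, trigger no warning, and in the TES arm are described as a check.
- **A paired analysis has its own bias.** An alarm from the randomised method may change the resection and so the outcome, turning a true positive into an apparent false positive. The other method is then scored against that altered outcome. Pooling the arms cancels this only if both alarms change outcomes to a similar extent, which the documents do not show.
- **A common 10-minute grid changes the question.** It estimates the accuracy of 10-minute monitoring, not of the 2-minute monitoring that is delivered.
- **The trial is exploratory, and technical detail is deferred to an SAP.** A supplementary analysis could sit there.

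The first four points stand. They limit the paired analysis to a supplementary role and rule it out as the sole basis for sizing. The last does not remove the conflict, because the article itself fixes both the test and the precision.

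**Conclusion.** The point holds as an unresolved unit of analysis. Sections 2.7.3, 2.11 and 2.13.1 cannot all stand as written.

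On the most natural reading, randomised method only, the primary comparison delivers widths of about 40 and 15 points (Wald) or 46 and 22 (score), against 29 and 13 stated. If both methods' readings enter from all patients, the stated widths are roughly right, but a test for independent proportions is not valid for the paired data.

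A within-patient comparison of readings that the trial already generates would have widths of about 27-31 and 9-14 points. Power for sensitivity would rise from about 35-40% to roughly 58-90%, depending on the McNemar version and the correlation.

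These figures rest on the accuracy and prevalence assumptions of section 2.11, on equal arms with the expected number of deficits, and on usable readings from both methods in all 110 patients. They measure precision only and make no allowance for the bias from acting on one method's alarms.

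**What to change.** 1. State in section 2.13.1 which readings enter the primary analysis: the randomised method only, or both methods in every patient.
2. Make section 2.11 agree. Either restate the widths for the unpaired analysis, about 46 and 22 points by the score method that matches the named test, or name a paired method and give its widths over a range of correlations.
3. If the between-arm test is kept, prespecify beside it a supplementary within-patient comparison of sensitivity among deficits and specificity among non-deficits. Use a Tango score interval or mid-p McNemar. Score both methods at baseline, at the 10-minute marks and at the final measurement. Report by arm first, then pooled.
4. Report the discordant-pair rate as one input to planning the confirmatory trial, not the sole basis.

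**Cost.** No extra patients or procedures. The second method's readings must be captured in the eCRF; whether they already are is not stated. The report must say that the grid describes 10-minute monitoring and that the pooled result balances the effect of acting on alarms only if that effect is similar for both methods.
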